### Blinding

Due to the nature of Tai Chi, participants and researchers are impossible to be blinded to the group assignment. To minimize bias, all outcomes will be measured at baseline, 12 weeks and 24 weeks after randomization by the same independent experienced assessors who are blinded to the allocation. After completing the statistical analyses, the group assignment will be revealed by the project manager.

### Withdrawal criteria and management

Participants will be allowed or required to withdraw from the trial if:
participants developing a serious disease which is not suitable to continue in the investigator’s opinion;seriously adverse events happen;participants request to withdraw from the trial.

The reasons and exit time will be recorded in standard case report forms (CRF).

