### Outcome measurements

#### Primary outcome

The primary outcome in our study is the change in average 24-h SBP between baseline and 12-week after randomization. Ambulatory blood pressure monitoring (ABPM) will be used to assess the BP level. Participants will wear ABPM kit (Space Labs Medical, ABP Monitor 90,217, Redmond, WA, USA) and maintain their usual activities during the monitoring period, while avoiding strenuous exercise. During a 24-h monitoring period, automatic inflation measurement will be taken every 15 min during daytime (07:00 to 22:59) and every 30 min during night-time (22:59 to 07:00). The 24-h ABPM will be measured at baseline, 12 weeks and 24 weeks after randomization. Participants will be asked to record the time to wake up and go to bed in their self-dairies.

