#### Attendance and drop-outs

The attendance of each participants will be checked and recorded in the CRF. Drop-outs from causes such as house moving, onset of severe diseases, or other medical complications are unavoidable, all the details will be recorded in the CRF.

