### Statistical analysis

The statistical analysis will be carried out using SPSS statistical package (version 25.0). Data will expressed as mean ± standard deviations. All primary and secondary analyses will be analyzed based on intention-to-treat. Missing data will be filled by Last Observation Carry Forward rules. Demographic characteristics and other baseline values will be described using descriptive statistics. Baseline characteristics of participants will be compared using chi-square test for enumeration data and one-way analysis of variance for continuous variables. For the primary outcome, we will run a comparison between Tai Chi group, walking group and waiting list control group to figure out whether exercise is more effective for this condition. We will then run another comparison between Tai Chi group and walking group to figure out whether Tai Chi is more efficacious for hypertension. The above analysis will be performed using the ANCOVA model, age, pre-intervention BP, duration of hypertension, and family history of hypertension will be used as covariate [45]. Difference between the groups was calculated as mean differences or odds ratios alongside with their 95% confidence intervals. Multiple comparisons between the groups will be adjusted according to the Bonferroni correction method. The correlational analysis of BP and endothelial function factors will be conducted using Chi-square test. We will perform subgroup analyses based on whether patients are on antihypertensive medication to separate the effect size of Tai Chi.

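### Withdrawal after a serious adverse event or serious disease is from the trial, not from the exercise programme; this undermines intention-to-treat, and exits before week 12 become zero change on the primary outcome

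*Protocol article*

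**What the plan says.** The Withdrawal criteria and management section of the protocol article begins "Participants will be allowed or required to withdraw from the trial if" and gives three reasons. The first is "participants developing a serious disease which is not suitable to continue in the investigator’s opinion". The second, with no qualifier, is "seriously adverse events happen". The third is the participant's own request. The only items the section names for recording are the reason and time of exit.

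Attendance and drop-outs places the same kind of event among the losses: "Drop-outs from causes such as house moving, onset of severe diseases, or other medical complications are unavoidable".

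Statistical analysis states "All primary and secondary analyses will be analyzed based on intention-to-treat" and, for gaps, "Missing data will be filled by Last Observation Carry Forward rules". The endpoint is fixed under Primary outcome: "The primary outcome in our study is the change in average 24-h SBP between baseline and 12-week after randomization". That section schedules ambulatory monitoring at baseline, week 12 and week 24 only.

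Two other sections point towards complete follow-up. Blinding says that all outcomes are measured at baseline, 12 weeks and 24 weeks. Safety monitoring says that adverse events are recorded throughout the observation period.

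**The concern.** The rule works at the level of the trial. The article does not distinguish a participant who stops exercising from one who leaves follow-up. The rule also covers the waiting-list arm, which has no exercise to stop during the intervention period, so there it can only mean leaving follow-up.

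Intention-to-treat is most useful when outcomes are observed for everyone randomised, whatever happened to them afterwards. A rule that can require exit after a serious event creates missing data for reasons tied to health, which may be related to blood pressure. The analysis then fills the gap with a carried-forward value. Adverse events that occur after the exit may also go unrecorded. Outcomes not collected cannot be recovered by a later analysis plan, so the place to settle this is the protocol.

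**Working it through.** **Step 1: what the sections imply together.**

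- Withdrawal criteria and management: exit is from the trial, permitted or required, with the reason and time recorded. No later assessment is mentioned.
- Attendance and drop-outs: severe disease and medical complications are drop-outs.
- Blinding and Safety monitoring: outcomes at 12 and 24 weeks, and adverse events throughout.
- Statistical analysis: all analyses by intention-to-treat, gaps filled by LOCF.

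The first two read as an end to follow-up. The third assumes that follow-up continues. The fourth keeps the participant in the analysis either way, with an imputed value if follow-up ended.

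**Step 2: what LOCF does, by time of exit.**

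- Exit before week 12, ambulatory BP: the last value is baseline, so primary change = baseline - baseline = 0 exactly.
- Exit before week 12, SF-36 and endothelial markers (measured at baseline and week 12 only): also zero change.
- Exit after the week-12 visit: the primary outcome is already observed. The week-12 ambulatory value is carried to week 24, which need not be zero change.
- Home BP (weekly): the last weekly reading is carried, which need not be the baseline value.

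**Step 3: size.** The plan gives no figure for exits under this rule. Its only attrition figure is the 20% in Sample size, which covers all causes, house moving included. The illustration below therefore rests on assumptions.

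Let d be the share of an arm that leaves before week 12, S the mean change of those who stay and L the true mean change of those who leave. For unadjusted arm means:

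- mean under LOCF = (1 - d) x S
- true mean = (1 - d) x S + d x L
- error = LOCF mean - true mean = -d x L

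Take S = -13.33 mmHg, reading the first planning figure in Sample size as the Tai Chi change. Assume d = 5%, 10% or 20%, and L = -13.33 (leavers like stayers) or +5 (leavers get worse).

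| d | LOCF mean | true mean, L = -13.33 | error | true mean, L = +5 | error |
|---|---|---|---|---|---|
| 5% | -12.66 | -13.33 | +0.67 | -12.41 | -0.25 |
| 10% | -12.00 | -13.33 | +1.33 | -11.50 | -0.50 |
| 20% | -10.66 | -13.33 | +2.67 | -9.66 | -1.00 |

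For example, at d = 10% the LOCF mean is 0.9 x (-13.33) = -12.00. With L = +5 the true mean is -12.00 + 0.1 x 5 = -11.50, so the error is -0.50.

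The 20% row is extreme, because it attributes the whole all-cause allowance to exits before week 12. Against the planning SD of 20, the largest error shown is 2.67 / 20 = 0.13 SD.

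**Step 4: direction.** The sign of the error is opposite to the sign of L, which is not known. For a difference between two arms, the error is -(d1 x L1 - d2 x L2). It can favour either arm or cancel. The planned ANCOVA adjusts for baseline BP and other covariates, so adjusted means will differ somewhat from these. The imputed zero still enters the model as the outcome.

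**The case against.** The strongest case on the other side is that the article never says measurement stops at withdrawal. It is a condensed account, and the difference between discontinuing and withdrawing often sits in the full protocol, the operating procedures or the CRF. Blinding and Safety monitoring, taken at face value, promise continued collection. Much of the harm described also comes from LOCF rather than from the withdrawal rule.

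Part of this stands. Ending outcome collection is an inference, though it is the natural meaning of leaving the trial with an exit time, and the drop-out section supports it. The point does not rest on silence: the article states a trial-level rule that does not fit its own statements on follow-up. A different imputation method would change the filled-in value but would not restore the missing observation.

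Four stronger readings are tempting, and the article does not support them:

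- *The rule contradicts intention-to-treat.* LOCF keeps these participants in the analysis in their assigned arm. What is lost is their observed outcome.
- *Everyone with such an event must leave.* The rule permits as well as requires, and for serious disease it depends on the investigator's opinion.
- *A harm in an exercise arm is hidden.* The triggering event is recorded, under both the withdrawal and the safety sections. At most, later events are missed. LOCF acts on missing measurements, not on adverse-event records.
- *The bias flatters Tai Chi, or a set number of participants per arm would be regained.* Nothing in the article gives the number of such exits, their split between arms or the leavers' true change. The 20% allowance cannot be divided by cause.

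**Conclusion.** The point holds in a limited form. As written, the withdrawal and drop-out sections lead to missing outcomes for health-related reasons. That weakens the intention-to-treat analysis and sits badly with the promise of 12- and 24-week outcomes and continuous adverse-event recording. For ambulatory BP, an exit before week 12 becomes a primary change of exactly zero; that follows from the visit schedule and the LOCF rule, provided follow-up ends at exit. It does not extend to later exits or to weekly home BP.

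The size and direction of the resulting bias are unknown. The figures of roughly -1.0 to +2.7 mmHg in one arm's mean show only the range under the assumed shares and assumed true changes. The case for acting does not depend on them: the change is cheap, and it can be made only before the outcomes are lost.

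**What to change.** Reconcile Blinding, Withdrawal criteria and management, Attendance and drop-outs, Safety monitoring and Statistical analysis, as follows:

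- State that stopping the assigned intervention is not the same as leaving follow-up. Leave the clinical criteria and the investigator's judgement as they are.
- Invite every participant who has not withdrawn consent to follow-up, and is able to attend, to the scheduled 12- and 24-week assessments.
- Record adverse events to week 24 for these participants.
- Make *stopped intervention* and *left follow-up* separate CRF items, each with its own date and reason.

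If the full protocol already makes this distinction, aligning the wording of these sections is enough. The cost is protocol and CRF wording, plus some effort to bring people back to visits already in the schedule. Some will still decline or be unable to attend, so missing data will be reduced rather than removed.

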### Interventions

All participants will be asked to maintain usual diet and lifestyle. We will use CRF to record session attendance of participants in Tai Chi group and walking group. In order to monitor the progress, we will collect and analyze the session attendance as well as the self-reported diaries.

#### Tai Chi exercise

Participants in Tai Chi group will be firstly instructed Yang style 24-form Tai Chi by the coaches with at least 5 years of teaching experience during the run-in period. After 3 days of teaching, coaches will assess the qualification of each participants based on: (1) accuracy of movement; (2) coordination and continuity of movement; (3) pauses times. Participants whose fluency and accuracy of Tai Chi movement reach over 60% with less than 5 times of pauses will be considered to be qualified. Unqualified patients will continue a 3-day teaching and a secondary evaluation. During the intervention period, qualified participants will receive a group-format exercise program, 3 sessions per week for 12 weeks. Each session will last 60 min, including a 10-min warm-up, a 40-min Tai Chi practice and a 10-min cool-down.

#### Walking exercise

Using aerobic exercise to reduces BP has been confirmed [35, 36] and recommended in hypertension management guidelines [32, 37]. Walking is a simple and easy aerobic exercise for the elderly to do. We will use walking with targeted intensity as an active controlled. Walking group will be asked to walk, 3 sessions per week for 12 weeks. Each session will last 60 min, including a 10-min warm-up, a 40-min walking and a 10-min cool-down. To ensure the compliance of exercise, participants will be asked to record the start and end time of each exercise session in self-reported diaries.

#### Exercise intensity of Tai Chi and walking

Studies showed that Tai Chi is an aerobic exercise with moderate intensity [13, 38, 39]. In order to achieve the comparability of Tai Chi group and walking group, we will use fitness tracker (HUAWEI HONOR 3, HUAWEI TECHNOLOGIES CO., LTD., China) to record participants’ heart rate during exercises to estimate exercise intensity in accordance with the definition of American College of Sports Medicine of moderate intensity aerobic exercise [40]. The target intensity is 64–76% of maximal heart rate (220-the person’s age). To ensure that participants in Tai Chi group and walking group exercised with the intended intensity throughout the training period, exercise intensity will be calculated and adjusted for 3 times during intervention periods (between weeks 1 to 4, 4 to 8, and 8 to 12).

#### Waiting list

Participants in waiting-list group will not receive any interventions and/or exercise training during the intervention period. They will give an option to receive Tai Chi training after follow-up period.

### Baseline assessment

The participants will undergo baseline assessment before intervention. A descriptive exploratory questionnaire will be administered to collect information as follows: (1) demographic and socioeconomic variables (gender, age, socioeconomic status, and education); (2) behavioral variables (physical activity, smoking, and alcohol consumption); (3) anthropometric variables (bodyweight, height, and waist circumference); (4) clinical variables (endothelial function and clinic BP).

### Outcome measurements

#### Primary outcome

The primary outcome in our study is the change in average 24-h SBP between baseline and 12-week after randomization. Ambulatory blood pressure monitoring (ABPM) will be used to assess the BP level. Participants will wear ABPM kit (Space Labs Medical, ABP Monitor 90,217, Redmond, WA, USA) and maintain their usual activities during the monitoring period, while avoiding strenuous exercise. During a 24-h monitoring period, automatic inflation measurement will be taken every 15 min during daytime (07:00 to 22:59) and every 30 min during night-time (22:59 to 07:00). The 24-h ABPM will be measured at baseline, 12 weeks and 24 weeks after randomization. Participants will be asked to record the time to wake up and go to bed in their self-dairies.

#### Secondary outcomes

The average 24-h DBP, average SBP and average DBP during the daytime and night-time, BP variability, SBP load and DBP load, circadian rhythm of BP, and morning BP surge measured by ABPM will be considered as secondary outcomes.

Endothelial dysfunction is associated with hypertension and its presence correlates with target organ damage. Furthermore, endothelial dysfunction may be both a cause and a consequence of hypertension [41]. Therefore, the change of serum concentrations of Nitric Oxide (NO), endothelin (ET), thromboxane A2(TXA2), vascular endothelial growth factor (VEGF) will be tested to measure the endothelial function using commercial ELISA kits (Bender Med-Systems, Vienna, Austria). Blood samples of participants will be collected at baseline and 12 weeks after randomization.

Home blood pressure monitoring (HBPM) is a self-monitoring tool that can be incorporated into the care for patients with hypertension. Patients will use automated blood pressure monitors (AND, UA-767PBT; Shenzhen, China) to measure BP at home. HBPM will be conducted according to 2019 Chinese Hypertension League guidelines on home blood pressure monitoring [42] during the whole trial. At baseline, patients will measure BP at home every morning (6:00–9:00) and evening (18:00–21:00), 3 times per measurement for 7 days. During intervention and follow-up, patients will measure BP at home every Monday morning (6:00–9:00) and evening (18,00–21:00), 3 times per measurement [42]. Meanwhile, participants will be asked to record BP value in their self-dairies.

Changes in patients’ health-related quality of life will also be assessed according to the Medical Outcomes Study 36-Item Short Form (SF-36) questionnaire Chinese version [43]. This scale contains eight dimensions (physical function, role physical, bodily pain, general health, vitality, social function, role emotional, mental health) and two summary components (physical and mental), with score from 0 to 100. High scores indicate a better quality of life. SF-36 will be measured at baseline and 12 weeks after randomization.

For participants with antihypertensive medication, they will be asked to record the frequency, dosage and types of medication in their self-dairies.

#### Attendance and drop-outs

The attendance of each participants will be checked and recorded in the CRF. Drop-outs from causes such as house moving, onset of severe diseases, or other medical complications are unavoidable, all the details will be recorded in the CRF.

#### Safety monitoring

Adverse events are defined as any unexpected or uncomfortable signs, symptoms, or diseases. These adverse events include falling, fainting and any injury related to exercise. If any adverse events happen during the entire observation period, all the details will be recorded in the CRF.

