**Methods:**

This is an open-label single-center randomized controlled trial with 3 parallel arms. We will compare Tai Chi with walking and waiting-list control. We will recruit 234 hypertensive patients with mild to moderate essential hypertension and randomly assign them to 3 different groups. Participants in Tai Chi group will receive a group-format Yang style 24-form Tai Chi exercise program, 3 sessions per week for 12 weeks. The walking group will be asked to walk, 3 sessions per week for 12 weeks. The waiting-list group will not receive any interventions and/or exercise training. The primary outcome is the change in average 24-h systolic blood pressure (SBP) between baseline and 12 weeks after randomization. The secondary outcomes include 24-h Diastolic Blood Pressure (DBP), average SBP and average DBP during the daytime and night-time, blood pressure (BP) variability, SBP load and DBP load, circadian rhythm of BP, and morning BP surge, endothelial functional indicators, home measured BP, quality of life, adverse events and so on.

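### Adverse events are recorded as they arise, with no common enquiry stated across arms, so unequal contact may bias the comparison toward more recorded events in Tai Chi than on the waiting list

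*Protocol article*

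**What the plan says.** The Methods part of the abstract ends its list of secondary outcomes with "endothelial functional indicators, home measured BP, quality of life, adverse events and so on". The Secondary outcomes section in the body does not repeat adverse events; they are covered under Safety monitoring.

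That section gives a general definition, "Adverse events are defined as any unexpected or uncomfortable signs, symptoms, or diseases", then some inclusions, "These adverse events include falling, fainting and any injury related to exercise", and then the recording rule, "If any adverse events happen during the entire observation period, all the details will be recorded in the CRF".

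Contact by arm is set out under Interventions:
- **Tai Chi:** after 3 days of coached teaching, repeated once for those who do not qualify, "qualified participants will receive a group-format exercise program, 3 sessions per week for 12 weeks".
- **Walking:** the same number of sessions, for which "participants will be asked to record the start and end time of each exercise session in self-reported diaries".
- **Waiting list:** participants "will not receive any interventions and/or exercise training during the intervention period".

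The Blinding section says that "all outcomes will be measured at baseline, 12 weeks and 24 weeks after randomization by the same independent experienced assessors", and that these assessors do not know the allocation. Statistical analysis covers all primary and secondary analyses by intention to treat and reports group differences as mean differences or odds ratios. It names no specific adverse event analysis.

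**The concern.** An event enters the case report form only if someone hears of it. A Tai Chi participant who falls at home has an occasion to mention it within days, at the next group session. A waiting-list participant with the same fall may have no stated study visit until week 12 or week 24, and must then recall it. Participants know their arm, which can add to the difference in what they choose to report.

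If events are caught more completely in Tai Chi than on the waiting list, a comparison of recorded events mixes harm with frequency of contact. The likely result is that Tai Chi looks less safe relative to no exercise than it is. This cannot be repaired once the data are in, because events that were never elicited leave no trace.

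Tai Chi against walking is less clear. Walkers have no stated group sessions, but their attendance is recorded, they wear heart-rate trackers, and their intensity is reviewed three times. Capture may differ there too, but the text does not settle by how much.

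**Working it through.** The plan states no adverse event rate, margin or power, so there is no figure to reproduce. The check counts the stated contacts and then asks what unequal capture would do.

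**Step 1. Stated contacts after randomisation** (Interventions; Design and setting; Blinding)

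| | Tai Chi | Walking | Waiting list |
|---|---|---|---|
| Exercise sessions | 3 × 12 = 36, group format | 3 × 12 = 36, logged by the participant | 0 |
| Teaching days | 3, or 3 + 3 = 6 | none stated | none |
| Outcome visits | 2 (weeks 12, 24) | 2 | 2 |
| Monday home blood pressure diary | yes | yes | yes |

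Sessions plus visits to week 24 come to 36 + 2 = 38 in Tai Chi against 2 on the waiting list. A coach's presence at the 36 Tai Chi sessions is a natural reading of the format, but it is not stated in so many words.

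**Step 2. Is the diary a common channel for adverse events?** The listed diary contents are exercise times (Walking exercise), waking and bed times (Primary outcome), and home readings and medication (Secondary outcomes). Adverse events are not among them.

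**Step 3. Effect of unequal capture.** Inputs: 78 participants per arm (Sample size). Assumed, because the document gives no figures: true risk p = 20% in both arms; capture 0.9 in Tai Chi; capture c of 0.9, 0.7 or 0.5 on the waiting list.

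Recorded risk = p × capture. Expected participants with a recorded event = 78 × recorded risk.

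- Tai Chi: 0.20 × 0.9 = 0.18; 78 × 0.18 = 14.0.
- Waiting list, c = 0.9: 0.18; 14.0; odds ratio 1.0.
- Waiting list, c = 0.7: 0.14; 10.9; odds ratio (0.18/0.82)/(0.14/0.86) = 1.35.
- Waiting list, c = 0.5: 0.10; 7.8; odds ratio (0.18/0.82)/(0.10/0.90) = 1.98.

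The ratio of recorded risks is 0.9/c whatever p is: 1.00, 1.29 and 1.80.

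**Step 4. How often would it show?** This uses exact binomial counts for the chance that the Tai Chi count exceeds the waiting-list count, and the power of a two-sided 5% comparison of two proportions.

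| True risk | Waiting-list capture | Chance Tai Chi count is higher | Chance of a significant excess |
|---|---|---|---|
| 10% | 0.9 | 0.44 | 2.5% |
| 10% | 0.7 | 0.62 | 7% |
| 10% | 0.5 | 0.80 | 16% |
| 20% | 0.9 | 0.46 | 2.5% |
| 20% | 0.7 | 0.72 | 10% |
| 20% | 0.5 | 0.91 | 30% |

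The direction is fixed whenever waiting-list capture is lower. The size depends wholly on the assumed capture.

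**The case against.** The strongest reply is that the article may simply not describe how events are elicited. Investigator training and quality control says staff are trained, under a standard operating procedure, to assess safety alongside the SF-36. The Blinding section has blinded assessors measuring all outcomes at three common times, which, if adverse events are an outcome, points to some shared assessment. The operating procedure and the content of the SPIRIT schedule are not shown. This stands as a reason not to claim that collection is purely passive. It does not remove the point. The one recording rule that is written is event-driven, two common visits do not offset 36 sessions against none, and the diary contents that are spelled out leave adverse events out.

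Four stronger readings are tempting but not supported.

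- A reader might infer that Tai Chi is bound to show more events. That requires lower capture on the waiting list, for which the document gives no figure. Even at 0.9 v 0.5 capture and 10% true risk, the excess appears in about 80% of trials.
- A reader might infer that the definition depends on exercise. It does not. Exercise injury is one inclusion under a general definition, and an injury from the programme is a real harm that should be counted.
- A reader might think a fall without injury is left to the recorder's judgement. Falling is expressly included, with no requirement of injury.
- A reader might think the hope, in the abstract and Discussion, that Tai Chi will prove acceptable rests on this comparison. No section makes that link.

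**Conclusion.** The point holds as a risk of unequal ascertainment, not as a demonstrated bias. It rests on three things in the text: adverse events are named as a secondary outcome (in the abstract), the stated recording rule is event-driven with no common enquiry, and stated contact is very unequal in an open-label trial. It also takes the secondary-outcome status, together with the general rule on reporting group differences, to mean that events will be compared between arms. That is a fair reading, but not an explicit statement.

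The likely direction is more recorded events in Tai Chi than on the waiting list. The size is unknown; the odds ratios of 1.0 to about 2.0 are illustrations under an assumed 20% true risk and assumed capture. The primary outcome is not affected. The matter is worth correcting because the remedy is cheap and only works if it is in place before data collection.

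**What to change.** Add one fixed question to the self-diary that accompanies the Monday home blood pressure readings, which the Secondary outcomes section asks of participants without distinction by arm. It would ask about any fall, faint, injury or new symptom since the previous Monday, whatever the cause, from randomisation to week 24. Have the blinded assessors ask the same question, covering the period since the last visit, at weeks 12 and 24.

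Base the between-arm comparison on events collected in this uniform way. Record relatedness to exercise as a separate field. Report events volunteered at sessions separately, so that they remain visible without entering the comparison. If the operating procedure already contains such an enquiry, one sentence under Safety monitoring saying so would be enough.

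The cost is one diary line and one case report form field, with no extra visits. The downside is a higher absolute count of minor events and slightly more diary burden. With equal capture and equal true risk, the expected ratio of recorded risks returns to 0.9/0.9 = 1.00.
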